### Study sample

#### Participant inclusion and exclusion criteria

Patients with acute suicidal thoughts or behaviours are included who fluently speak and read the German language and who are capable to agree to participate in the study and provide written informed consent. Most patients are expected to suffer from affective and/or anxiety disorders and/or personality disorders. This study is only treating suicidal inpatients. The consent, legal capacity, and cognitive capacities are clinically evaluated. When participation is clinically judged to be contraindicated for a particular patient, they are excluded from the study.

Patients are also excluded who are chronically suicidal and/or have been treated in an inpatient psychiatric setting for a total of more than 12 weeks within the last 12 months, or who have been admitted more than 6 times during this period, or who live in an assisted living facility. In addition, patients with a psychotic disorder during the last 12 months, an eating disorder with BMI < 16 and/or a current substance dependence are excluded. Substance abuse or previous substance dependence are not exclusion criteria. Patients who are currently suffering from psychotic symptoms as part of an underlying depressive disorder are also excluded, as are patients with developmental disabilities, dementia or an organic condition. Patients are also excluded, who, at the time of admission, have already planned further long-term inpatient or day-clinic treatment to continue after crisis intervention therapy without being discharged in the meantime, as well as those, who have to be treated on our crisis ward for longer than 40 days. However, the duration of the treatment must be at least 10 days in order to ensure that patients receive a sufficient extent of treatment (at least three sessions following the admission interview). The exclusion criteria are established at the time of admission (t_1_) and validated by using the diagnostic interview any few days later. Patients who are committed against their will as per civil legal requirements (PsychKG of the federal state of North Rhine-Westphalia or the nationwide valid law of care) do not take part in the study.

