#### Subject withdrawal criteria and procedures

In the informed consent procedure, participants are informed from their therapists that they can withdraw their consent from study participation at any time without providing reasons and with no negative consequences. However, clinical staff will ask participants to share their reasons for withdrawal in order to identify any adverse impact of study procedures and to identify any difficulties experienced by subjects during the trial. Withdrawn participants will have the opportunity to continue a regular crisis therapy on the ward if this is clinically indicated.

In addition, participants can be withdrawn from the trial by the investigators, if an exclusion-criteria is found after initial inclusion either during the screening-process or by clinical assessment. For example, a patient who develops psychotic symptoms during the course of treatment may be withdrawn from the study. The participant is then excluded from the trial and continue with a regular treatment in the clinic.

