### Diagnosis

#### Structured clinical interview for DSM-IV Axis I & Axis II

##### SCID- I & SCID-II

The SCID-I is a diagnostic instrument based on diagnostic criteria for Axis I disorders found in the *Diagnostic and Statistical Manual of Mental Disorders*, Fourth Edition (DSM-IV-TR [41–43];). The SCID has been shown to have good reliability with kappa values ranging from .04 to .84; there is an overall mean of .61 for all disorders across a large number of samples. Test-retest reliabilities for disorders in psychiatric patients range from .54 to .84 with a mean of .73. Additionally, the *Structured Clinical Interview for DSM-IV Axis II* was used to identify participants with any personality disorder, because of the higher suicide risk associated with personality disorders, which is particularly true for patients with borderline personality disorder [44]. The SCID interviews will be conducted after the baseline assessment within the first days of study treatment.

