There are no mandatory homework assignments during a CAMS course of care. The duration of CAMS-guided care is dependent on the treatment progress and varies between patients. The treatment is concluded when the clinician and the patient agree that the acute danger of a suicidal act is eliminated, adaptive coping skills are developed while the patient scores him/herself below 3 on subjective suicidal risk rating (on a 5-point scale) and that they are managing any suicidal thoughts or feelings while remaining behaviorally stable which may trigger discharge from the inpatient setting. In the present RCT, cases who have received between 4 and 9 CAMS sessions including the initial session will be analysed. See Appendix 2 for the complete CAMS Material.

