### Statistics

#### Power analysis and sample size calculation

An a priori power analysis by using G*Power was carried out to determine the sample size [47]. On the basis of the available literature, we expect an average effect size (comparison of CAMS versus TAU with regard to the reduction of suicidal tendencies) of Cohen’s d = 1. Here we refer to the study by Ellis (2015), which is rather comparable [21]. The author reports a pre-post effect size of d = 1.72 for CAMS (measured by the BSS) and of d = 0.71 for TAU. Although the interaction effect was not reported we assume it to be about d = 1.

Taking into account a probability of α error = 5% (one-sided) and a power of 1 - β = 80%, the total sample size of 48 participants, i.e. 24 per group. For compensating participants who withdraw their consent we plan 30 subjects per group. Assuming that after the first diagnostic examination 50% are not eligible for inclusion into the study due to non-existent inclusion criteria or exclusion criteria and 20% discontinue treatment in the course of the study or are excluded due to further inpatient treatment, it is to be expected, that 144 patients have to be interviewed, of whose 72 patients (36 per group) are randomly assigned to CAMS intervention (36 subjects) and a TAU (36 subjects), respectively, in order to achieve the targeted number of *N* = 2 × 30 in the intent to treat sample.

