### Data analyses

#### Statistical analyses

The analysis of this study will be calculated as a mixed-effects model with the BSS total symptom score as the outcome variable. Mixed models are especially suited for longitudinal studies as they can deal with a correlated data structure and can analyze all cases and data points, even if missing values occur in the course of the trial. In detail, participants will be modeled as a random factor, while time and intervention (CAMS vs. TAU) as well their interaction will be modeled as fixed factors. The hypothesis that CAMS is superior to TAU in the treatment of suicidal patients will be evaluated by the significance test of the interaction effect time × intervention.

In case of a significant interaction effect, two planned general linear hypotheses will be calculated as post-hoc tests for linear mixed effect models in order to test between-group differences at t_2_ and t_3_. *P*-values will be adjusted for multiple comparisons following the Holm procedure.

We will perform an intention-to-treat analyses, that is, all trial participants will be analyzed as randomized, even if they discontinue treatment or are unavailable for one or both of the follow-up interviews. The between-group effect size (Cohen’s d) will be calculated at each follow-up assessment (t_2_ and t_3_).

Continuous secondary outcome measures (BDI-II, SCL-18-Mini, B-RFL, D-STAR-P) are analyzed in the same way. In absence of a valid cut-off score for clinically significant change or treatment response of the BSS, the number of subjects with clinically significant improvement as well as worsening based on the reliable change index (RCI) will be compared between groups using χ2 –tests or Fisher’s exact tests. For this purpose, the RCI will be calculated based on the pre-treatment scores of the study sample. We will use two-tailed tests for statistical significance with alpha set at *P* < 0.05. Effect strength will be determined with Cohen’s d. All calculations will be performed using SPSS 20.0 computer software [48].

We also investigate whether there is a correlation between the number of sessions and the effect of the therapeutic treatment using a correlation analysis.

Interim analyses before the completion of the investigations are not intended. Any potential deviations from the original statistical plan as defined in the study protocol will be described in protocol amendments as well as in the final study report.

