### Safety and ethical aspects of the trial

#### Safety

CAMS previously has been shown to be an effective treatment model. In a pilot study from 2012, Ellis and colleagues found that CAMS was successfully implemented and accepted by both patients and clinicians within the frameworks of an inpatient settings and Ryberg and colleagues (2019) showed that CAMS was successfully implemented within a very broad psychiatric sample with a high symptom load which is probably comparable to our sample [19, 20]. On this basis we expect that CAMS most probably will be acceptable and feasible to the patients and therapists within our clinic. Psychological stress caused by the examination of the causes of suicidal tendencies within the treatment is possible. Negative emotions will occur in all suicidal patients, this is immanent to the symptoms and treatment situation. The team at the ward, on which the study is conducted, is specialized in the treatment of this group of patients. In the event of an increase in psychological stress, patients in emergency situations have nursing staff on the ward and doctors on duty outside regular working hours available at all times for supportive interventions. In an emergency, safety measures can also be initiated in an inpatient context. Patients would be excluded if therapists were given the impression that CAMS or E-TAU treatment is detrimental to the patient.

In the case of suicides in the course of treatment and study participation that may occur in such a high-risk group, these are documented by the therapists.

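### The CAMS section limits analysis to cases with 4 to 9 sessions, which contradicts the promised intention-to-treat analysis, and the sample labelled intention-to-treat is smaller than the number randomised

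*Protocol article*

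**What the plan says.** The Statistical analyses section commits to intention-to-treat: "all trial participants will be analyzed as randomized, even if they discontinue treatment or are unavailable for one or both of the follow-up interviews". The section on avoiding attrition bias repeats this and adds that patients will be followed up after they discontinue.

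The section describing CAMS says that in this trial "cases who have received between 4 and 9 CAMS sessions including the initial session will be analysed". It gives the sentence no label such as per-protocol or sensitivity. The E-TAU section gives a dose of three to nine sessions plus one later session, but does not say that analysis depends on it.

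The sample size section randomises 72 patients (36 per arm). It assumes that "20% discontinue treatment in the course of the study or are excluded due to further inpatient treatment" and expects 2 × 30 in what it calls the intention-to-treat sample.

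Two other sections allow removal after allocation. Under subject withdrawal, "participants can be withdrawn from the trial by the investigators, if an exclusion-criteria is found after initial inclusion". Under Safety, "Patients would be excluded if therapists were given the impression that CAMS or E-TAU treatment is detrimental to the patient". Neither says whether these patients stay in the analysis. The diagnostic check that can reveal an exclusion criterion comes after allocation: "The SCID interviews will be conducted after the baseline assessment within the first days of study treatment".

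**The concern.** An analyst cannot both include everyone as randomised and include only CAMS patients with 4 to 9 sessions. The second rule conditions on something that happens after randomisation. By the CAMS section's own account, the length of a CAMS course depends on progress, and the course ends when acute danger has passed and self-rated risk is low. Session count is therefore partly a result of change in suicidality, which is what the BSS measures.

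The mixed model does not repair this. It copes with missed visits by patients who remain in the dataset, not with patients taken out of it. Using the intention-to-treat name for a set that has already lost patients makes the slip easier. While both rules stand, the primary analysis set could also be chosen after the data are seen.

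**Working it through.** **1. The rules side by side.** Statistical analyses: all participants, as randomised, whatever treatment they received. CAMS section: cases with 4 to 9 sessions. E-TAU section: a dose range only. A CAMS patient with two or three sessions is in under the first rule and out under the second. An E-TAU patient with the same number is in under the first, and no rule puts that patient out.

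**2. The plan's own numbers.** 144 interviewed × 0.5 eligible = 72 randomised, which reproduces the stated figure. The stated intention-to-treat sample is 2 × 30 = 60. The gap is 72 − 60 = 12, and 12/72 = 16.7%. (The stated 20% loss would leave 72 × 0.8 = 57.6; 72 is 60 × 1.2.) The Abstract speaks of randomising 60, and Trial status ends recruitment at 30 per group, so the documents need a single number.

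**3. Does the 4–9 rule touch eligible patients?** Inputs: about two sessions a week (CAMS section), the initial session counted (the rule itself), and stays of 10 to 40 days (Trial design; eligibility criteria). Adding the initial session to the weekly ones, sessions = 1 + 2 × days/7:

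- 10 days: 1 + 2.9 = 3.9
- 13 days (ward mean, Study center): 1 + 3.7 = 4.7
- 28 days: 1 + 8 = 9
- 40 days: 1 + 11.4 = 12.4

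A stay at the lower limit falls just short of 4, and stays beyond about 28 days pass 9. Eligible patients can fall outside the range at both ends, although a stay of average length does not.

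**4. Possible size of the bias (illustration only).** The documents do not say how removal relates to outcome, so the correlation r between worse outcome and removal is an assumption, shown from 0 to 0.5. Setting: no true effect, 36 per arm, normal outcome with SD 1, two-sided 5% t-test, 20,000 simulated trials per row. Removed: 6 of 36 (16.7%) or 7 of 36 (nearest whole number to 20%).

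| Removed | r | CAMS only: shift (SD), type I error | Both arms alike: shift (SD), type I error |
|---|---|---|---|
| 6 | 0 | 0.00, 4.6% | 0.00, 4.9% |
| 6 | 0.3 | 0.09, 7.1% | 0.00, 5.6% |
| 6 | 0.5 | 0.14, 9.0% | 0.00, 5.4% |
| 7 | 0 | 0.00, 5.1% | 0.00, 5.2% |
| 7 | 0.3 | 0.10, 6.8% | 0.00, 5.4% |
| 7 | 0.5 | 0.16, 10.7% | 0.00, 6.2% |

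The large-sample formula, shift = r × φ(z)/(1 − f), where f is the fraction removed and z the normal quantile that cuts it off, agrees. With r = 0.5 it gives 0.150 SD for f = 0.167 and 0.175 SD for f = 0.20. The shifts shown favour CAMS because poor outcomes are removed. If improvers are removed instead, the sign reverses.

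**5. Does full intention-to-treat cost needed power?** Under the plan's own d = 1, with a two-sided 5% t-test, 30 per arm gives 96.8% and 36 per arm gives 98.7%. If 6 of 36 CAMS patients gained nothing (assumption), d = 30/36 = 0.83 and power is Φ(0.83 × √18 − 1.96), about 94%.

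**The case against.** The strongest defence is that the 4-session floor restates one shared by both arms. The eligibility section says that "the duration of the treatment must be at least 10 days in order to ensure that patients receive a sufficient extent of treatment", meaning at least three sessions after the admission interview. E-TAU patients are to receive as many sessions as CAMS patients, and therapy dropout is defined without distinction of arm. If losses then arise alike in both arms, the average shift is about zero, as the right-hand column shows. This stands as a limit on the size of the problem. It does not remove the contradiction, because a floor on treatment is not a rule on who is analysed. Likewise, if CAMS courses are in practice capped at nine sessions, the upper limit removes nobody, but the text does not say so.

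Four stronger readings are tempting and are not supported.

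- A reader might infer that the trial will have an inflated type I error in favour of CAMS. The expected loss is 36 to 30 in each arm, not in CAMS alone, and the correlations are assumed. The participant retention section says that discontinuation often accompanies spontaneous improvement, so bias could run against CAMS.
- A reader might infer that the average ward patient falls below 4 sessions, since 13/7 × 2 = 3.7. The rule counts the initial session, which gives 4.7, and 13 days is the mean over all ward admissions rather than trial patients.
- A reader might infer that the stay limits, late diagnostic exclusions and the therapist's impression of detriment are themselves analysis exclusions. The text does not say so. Eligibility is described as set at admission, the diagnostic examiner is blinded, and the intention-to-treat statements can be read as governing. The defect is that the sections are silent.
- A reader might infer that harmed patients leave the safety record. No section says this. Suicides are to be documented, and reasons for withdrawal are sought in order to identify adverse effects.

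**Conclusion.** The contradiction is real and lies in the article's current text, so a separate analysis plan would not remove it. Followed literally, the session rule replaces the randomised comparison with a completer comparison, stated for one arm. The sample size section compounds this by giving the intention-to-treat name to a set already 12 patients (16.7%) short of the number randomised, and the withdrawal and safety sections leave the analysis status of excluded patients open.

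The size and direction of any bias cannot be derived from the documents. Under the assumptions shown it runs from nothing (removal unrelated to outcome, or alike in both arms) to about 0.17 SD and a two-sided type I error of about 11% (removal from CAMS only, r = 0.5). The point needs correcting because the primary analysis set is not fixed, not because a given amount of bias has been shown.

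**What to change.** - Delete the 4-to-9-session rule as a condition of the primary analysis.
- Define the primary set as every randomised patient, in the allocated arm, with any BSS data.
- State that stopping study treatment, an exclusion criterion found late, length of stay or transfer to further inpatient care removes a patient neither from the analysis nor from attempted follow-up.
- Keep a session-based set only as a labelled per-protocol sensitivity analysis, with the same limits and counting rule in both arms.
- Correct the sample size section so that the intention-to-treat number equals the number randomised, and reconcile it with the Abstract and Trial status.

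The cost is wording, plus follow-up that the attrition section already intends. Recruitment began in March 2017 and was expected to end in autumn 2019, so some t2–t4 data from patients who had already stopped may not be recoverable. The estimate may be smaller than among completers. Clinical decisions about withdrawing a patient from treatment are unaffected.

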#### Enhanced-treatment as usual (E-TAU)

In addition to the clinic’s standard therapy services, which CAMS patients also receive, patients in the TAU condition also receive supportive, behavioural-therapeutic counselling comparable to the “dose” of CAMS guided care in the experimental arm of the RCT (at least three and up to nine 30–60-min sessions during treatment and one post-operative session). There is no predefined manual for the TAU treatment. In addition to establishing a viable therapeutic relationship and acute relief, diagnostic, psychoeducation and initial therapeutic steps, the planning of further treatment of the underlying mental disorders or life problem will be central. Depending on the current risk situation, the aim is to promote the patient’s safety, to encourage the patient to reflect and to build up confidence and motivation for treatment and the effecting of changes. Depending on the problem areas described by the patient, the practitioners independently determine the focal points and contents of the therapeutic sessions together with the patients. The therapists are free to choose methods and strategies to promote self-control and the use of social support as well as to learn strategies for emotional stabilisation.

An overview of the various modules of crisis intervention in E-TAU can be found in Fig. 3. To increase experimental internal validity, TAU in this study was “enhanced” (i.e., E-TAU). Patients in E-TAU receive as many treatment sessions as CAMS Patients, approximately 2 per week, so the amount of treatment is comparable in both conditions. Thus, E-TAU is designed to balance and minimize threats to both the internal and external validity of the study.

**Fig. 3 Fig3:**
[figure not shown]
Diagram showing contents of E-TAU treatment

#### Standard inpatient care (SIC)

SIC contains all non-specific therapy elements that are identical for both intervention groups. In addition to the individual psychotherapeutic sessions described above, there are also occasionally supportive consultations with the nursing staff. Longer individual nursing contacts due to crisis situations will be documented in number and length. A daily morning meeting takes place for all patients. Depending on the patient’s stability and wishes, an individual therapy plan is designed so that the patient can participate in additional offers such as body and movement therapy, Jacobson relaxation, music therapy, occupational therapy and offers from clinical social work and pastoral care. Weekly team meetings serve to exchange information on each individual patient between all the professional groups involved, and weekly visits by a senior physician also take place. The interventions are embedded in the context of a therapeutic environment that offers continuous care, supervision, and plenty of opportunities for spontaneous contact with fellow patients.

### Choice of comparator

The aim of this trial is to test the effectiveness of CAMS for suicidal inpatients on an acute crisis ward. For this purpose, it is necessary to compare CAMS as provided on the ward with the efficacy of the treatment that would be available without this module, i.e. a TAU condition. So far, no data exist regarding the effectiveness of TAU in this understudied population. As described above, TAU in this study was “enhanced” (i.e., E-TAU), which means that the treatment dose is comparable in both conditions, and multiples assessments further improve the patient’s experience, thereby increasing the internal validity of this RCT.

### Medications and treatments permitted/not permitted during the intervention

In both groups, patients receive medication according to their diagnosis and current symptoms, based on the clinical judgement of the senior physician (and following international guidelines). Benzodiazepines and medication on demand can also be used. All medication and changes in medication are recorded in both groups. We expect that medications will be equally represented in both arms as per randomization. In the follow-up assessments, we will determine which follow-up treatments the patients has received (e.g., outpatient psychotherapy or psychiatric treatment as well as any partial care or inpatient treatment).

